### Assessment instruments

#### Schedule for affective disorders and schizophrenia for school-age children-lifetime version (Kiddie-SADS-L)

The Kiddie-SADS-L can assess the current and history of mental disorders in children and adolescents, including behavioral disorders such as attention-deficit/hyperactivity disorder, opposition defiance disorder, and conduct disorder, as well as common psychopathological phenomena such as affective disorder, anxiety disorder, and psychotic disorder (39). It has content validity, the interrater consistency was 93–100%, and the test-retest reliability coefficient for common mental disorders ranged from 0.63 to 1.00 (40).

#### Yale global tic severity scale

The YGTSS was developed based on the Tourette Syndrome Global Scale and displayed very good internal consistency, interrater reliability, and convergent and divergent validity (41). Its total (motor + phonic) tic severity score can identify clinically meaningful exacerbations of tics. The YGTSS is the only scale for which cutoff values of score changes indicate clinically relevant exacerbations and treatment responses, making it the most suitable instrument for prospective follow-up in clinical observational longitudinal studies and therapeutic trials.

#### Premonitory urge for tic scale

The PUTS has been developed and has shown good psychometric properties (19). While this scale has been widely used in clinical research related to tics, the PUTS reports the feelings before tics and the corresponding severity but does not include the locations of PUs (42).

#### Children's Yale-Brown Obsessive-Compulsive scale

The CY-BOCS, designed for children, is a modified version of the Yale-Brown Obsessive-Compulsive Scale (Y-BOCS) (43). The CY-BOCS is a clinician-rated, semistructured instrument designed to assess the symptom severity of obsessions and compulsions. Each item is rated on a 5-point ordinal scale: 0 = none, 1 = mild, 2 = moderate, 3 = severe, and 4 = extreme. The total score is obtained by adding the scores for Items 1 through 10 (range = 0–40). The subscales of obsessions (Items 1 through 5) and compulsions (Items 6 through 10) each range from 0 to 20. A considerable body of data from around the world attests to the reliability and validity of the instrument in children with OCD. The adult version (Y-BOCS) has been translated into Chinese, with a Cronbach coefficient of 0.75 (44). However, evidence of the reliability and validity of the CY-BOCS in Chinese children and adolescents is lacking. In our previous study, we used it as a tool for TS evaluation. We included 200 samples, and the Klezbach coefficient of the scale in children with tic symptoms was more than 0.85.

#### Clinical global impression

The CGI provided a brief, stand-alone assessment of the psychiatrist's view of the patient's global functioning before and after initiating study treatment (45). This scale mostly assesses the severity of psychopathology and changes from the initiation of treatment, resulting in an efficacy index.

#### Five facet mindfulness questionnaire

The FFMQ is a 39-item self-report measure (46) that is used to evaluate the internal perception of self-report to clarify the changes in subjective perception. The items on this scale focus on self-awareness of internal feelings, such as “when I walk, I deliberately pay attention to the feelings in physical movement”; or focus on emotions, such as “I focus on how my emotions affect my thoughts and behavior”.

#### Screening child anxiety-related emotional disorders

The SCARED is a self-reported measurement tool specifically used to measure anxiety symptoms of children and adolescents, including the five factors of somatic/panic disorder, generalized anxiety disorder, separation anxiety disorder, social phobia, and school phobia, with a total of 41 items (47). The participants rated the frequency of each symptom on a 3-point scale of 0–2, and the average score of the relevant items was calculated as the specific anxiety symptom score and total anxiety score. Previous studies have shown that the scale has been widely used in the screening of children's anxiety and has good reliability and validity in the context of Chinese culture (48).

#### Wechsler intelligence scale

The Chinese version of the Wechsler Intelligence Scale for children (49) was used to evaluate the participants' intelligence quotient (IQ). The scale has a national norm. It is divided into urban versions and rural versions. The split-half reliability of each subtest score is high (the split-half correlation coefficient is ~0.8), the IQ split-half reliability is above 0.9, and the test-retest reliability range is 0.59–0.86 (50). It has also been shown to have structural validity. In China, this is an important tool for assessing children's IQ level.

### Assessment procedures

The clinical evaluation process will mainly be completed by two attending child psychiatrists. Before the formal evaluation, an evaluation of the consistency between raters will be completed. The clinical evaluation will be carried out only after the consistency of the raters is above 0.85. The time points for the evaluation mainly included the baseline test, within 1 week after the completion of eight sessions of intervention, and at the end of 1 month after eight sessions of intervention. The patients will be followed up at the end of 3 and 6 months after the eight sessions of intervention. For more details, see Figure 1.

**Figure 1 F1:**
[figure not shown]
Proposed procedure and flow of participants of the study. IQ, Intelligence quotient; TS, Tourette syndrome; MHRT, Mindfulness-based habitual reversal training; HRT, Habit reversal training; PST, psychoeducation and supportive therapy; HC, healthy controls; Kiddie-SADS-L, Schedule for Affective Disorders and Schizophrenia for School-Age Children-Lifetime Version; YGTSS, Yale Global Tic Severity Scale; PUTS, Premonitory Urge for Tic Scale; CY-BOCS, Children's Yale-Brown Obsessive-Compulsive Scale; CGI, Clinical Global Impression; FFMQ, Five Facet Mindfulness Questionnaire; SCARED, Screening child anxiety-related emotional disorders; WIS, Wechsler Intelligence Scale.

This study is a single-blind RCT. Each child was randomized to either an MHRT, HRT or PST. All groups were described to participants as active interventions with potential but unknown benefits. Assessors were blinded to the treatment conditions.

### Interventions for the different groups

There are three main types of intervention techniques used in this study: traditional HRT, MHRT, and PST. The intervention includes a total of eight sessions, and a consistent time frame will be used with each intervention method. More details can be seen in Figure 2.

**Figure 2 F2:**
[figure not shown]
MHRT and HRT Process. Only the MHRT group received mindfulness training.

The kind of mindfulness meditation used in the clinical setting is a secularized amalgamation of Buddhist contemplative practices (51). Mindfulness meditation is given during all sessions. The content is focused on learning how to mindfully attend to body sensations, especially PUs. Mindfulness training includes mindfulness of the breath, body scanning, sitting meditation, and mindful movement in the consulting room. The whole process lasted 15 min in each session. Additionally, the training recommends that participants apply these mindful practices in daily life. Mindfulness modules are applied to aid participants in recognizing PUs with the ultimate effect of being able to engage in competing responses in a more accessible manner. Details on the components of the mindfulness training are provided in Table 1.

**Table 1 T1:** Content of mindfulness training in MHRT.

**Session**	**Thematic curriculum**	**Mindfulness modules**
1	Understand mindfulness	1. What is mindfulness; 2. How can mindfulness be useful for addressing tic symptoms; 3. Body scan; 4. Homework: pausing during daily life.
2	Be in the present	1. Be in the present; 2. Tic and unpleasant events journal; 3. Mindful breathing; 4. Homework: mindful breathing and mindful walking in daily life.
3	Be mindful of PUs	1. Recognize the PUs and tic; 2. Mindful breathing; 3. Mindful stretching; 4. Homework: 3-min breathing space in daily life.
4	Accept difficulties in Competing Response Training	1. Difficulties journal; 2. Learn to accept difficulties; Mindful meditation (be with difficulties); 3. Homework: 3-min breathing space in daily life
5	Emotions and stress responses	1. Recognize mood without judgment; 2. Let thoughts about mood be; 3. Mindful meditation (be with thoughts about mood); 4. Homework: pausing during daily life
6	Enjoy daily happiness	1. Be mindful of happiness; 2. Pleasant events journal; Mindful meditation (be with daily happiness); 3. Homework: 3-min breathing space in daily life
7	Discuss relapse prevention strategies	1. Feel PUs mindfully; 2. Be mindful of emotions; 3. Discussion relapse prevention strategies; 4. Homework: 3-min breathing space in daily life.
8	Continued mindfulness practice	1. Discussion on awareness of PUs and emotions; 2. Consider continued mindfulness practice.

PUs, premonitory urges; MHRT, Mindfulness-based habitual reversal training.

Traditional HRT includes general awareness training, competitive response training, relaxation training, and homework (20). Although traditional HRT includes relaxation techniques, diaphragmatic breathing exercises and progressive muscle relaxation, there are also key differences between MHRT and traditional HRT. These differences are reflected in practice time and content.

PST is a relatively basic treatment among psychological and behavioral interventions for TS (52) and mainly includes two aspects. First, parents are trained in topics including popular scientific perspectives of the disease, how to analyze factors that induce exacerbation of tic symptoms, and how to encourage children to deal with the disease for 20–30 min. The second aspect involves communication and interactions with the children. The conversation with the children lasted for more than 30 min. The main contents include the feeling and understanding of tics, helping children deal with accompanying emotions, and evaluating and addressing shame and stigma. The intervention times were consistent with the other two therapies.

### MRI scanning

#### Basic information for MRI scanning

Brain imaging data from all participants will be acquired using a 3.0 T scanner (MR-750, General Electric, USA). Before data collection, participants will become familiar with the scanning environment. Then, participants are placed supine, asked to remain awake, and placed into the scanner. Head motion will be minimized by inserting special-purpose foam pads. During this process, the participants needed to keep their eyes closed and their bodies motionless.

#### MRI scanning sequence

T1-weighted images will be acquired using a sequence with the following parameters: repetition time (TR) = 7 ms, echo time (TE) = 3.2 ms, flip angle = 8 degrees, resolution = 240 × 240, slices = 192, and slice thickness = 1 mm. Functional whole-brain images will be acquired using an echo planar imaging sequence (TR = 2,280 ms, TE = 30 ms, image matrix = 64 × 64, FOV = 224 mm, flip angle = 80°, slice thickness = 3 mm, distance factor = 17%, voxel size = 3.5 × 3.5 × 3.0 mm, and 36 axial slices). A total of 80 images aligned to PC–AC will be acquired per functional imaging block.

#### Preprocessing

Processing steps will use MATLAB and Data Processing Assistant for Resting State fMRI (DPARSF) (53). The first five volumes will be discarded to allow the magnetization to approach a dynamic equilibrium and for the subjects to get used to the scanner noise. Data preprocessing, including slice timing, head motion correction (a least squares approach and a 6-parameter spatial transformation) and spatial normalization to the Montreal Neurological Institute (MNI) template (resampling eight voxel sizes of 3 × 3 × 3 mm), will be performed. A spatial filter of 4-mm FWHM (full-width at half maximum) will be used. Participants showing head motion above 3.5 mm of maximal translation (in any direction of x, y or z) and 1.0° of maximal rotation throughout the course of the scan will rule out subsequent statistical analysis.

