#### Construction of the network

The template of the neuroimaging research laboratory of Stanford University (Functional Imaging in Neuropsychiatric Disorders Lab website; http://findlab.stanford.edu/functional_ROIs.html) will be used to explore the DMN and SN (54). For the ROIs of the DMN and SN, see Supplementary Tables S1, S2.

We will use the Brain Connectivity Toolbox to extract the connection information between various brain regions and draw the connection diagram at the macro level. This will be used to quantitatively describe the structure, function, connection model and topological characteristics of the human brain network. We will mainly focus on the brain regions related to PUs: the insula, ACC, supplementary motor area (SMA) and prefrontal cortex. We will take the DMN and SN as the main brain function networks to consider.

Degree, global efficiency, local efficiency, path lengths and cluster coefficients will be used to investigate the relationships between the changes in these two brain functional networks and the improvements in tics and PUs and to clarify the possible brain mechanisms underlying the effects of MHRT from the perspective of brain functional networks. We will assess global network integration, segregation and connectivity between modules using the following measures for the DMN and SN: (1) degree: number of edges connected to a node; (2) global efficiency: global transmission capacity of the network; (3) cluster coefficient: degree of network collectivization; (4) local efficiency: nodal connections to within-network nodes; (5) path length: optimal path from one node to another. To assess the reliability of the results and enhance comparability with previous research, exploratory analyses on the absolute Fisher r-to-z transformed Pearson correlation connectivity matrices will be performed using the same graph indices. The calculation formulas for these parameters are presented in Supplementary Figure S2.

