### Statistical analysis

Measures will be analyzed using IBM SPSS Statistics version 22 (IBM, Armonk, NY, United States).

First, the efficacy of MHRT will be tested using repeated measures analysis of variance (ANOVA). A 3 × 3 mixed design will be used to examine the main effects of group (MHRT, HRT or PST) as a between-subjects factor and time point as a within-subjects factor, as well as interaction effects. Second, for the imaging study, we will assess connectivity between the DMN and SN and compute the average Fisher r-to-z transformed Pearson correlations of the resting-state fMRI time-series between the nodes that belong to these resting-state networks. Pearson correlations will be used to replicate earlier functional connectivity studies. For analysis of the abovementioned neuroimaging indices, we will use univariate mixed-model analyses to assess the effects of MHRT and HRT. We will use the after-training outcomes as dependent variables, the group (MHRT, HRT, PST, and HC) as the independent variable and the baseline measure of the outcome as a covariate. We will also perform these analyses correcting for age, years of education and sex.

Measurement data will be presented as the mean ± standard deviation (x ± s). The demographic and efficacy indices of the three intervention groups before and after the intervention will be compared by multifactor analysis of variance (measurement data), and repeated measures analysis of variance and paired *t*-tests will be used for comparisons between multiple groups and before and after the intervention. In addition, we regarded at least 30% changes in YGTSS scores $\left[(\frac{\mathrm{Pr}e_{\left(YGTSS\right)}-Post_{\left(YGTSS\right)}}{\mathrm{Pr}e_{\left(YGTSS\right)}}\right)\times 100\%]$ as the clinically meaningful level.

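### The motion exclusion is worded so that both limits must be exceeded, and the imaging model has no head-motion term, so an arm difference in motion after training could pass for a network effect

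*Protocol article*

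**What the plan says.** **Exclusion rule (Protocol article, Preprocessing).** The rule applies to "Participants showing head motion above 3.5 mm of maximal translation (in any direction of x, y or z) and 1.0° of maximal rotation", and its consequence is that such motion "throughout the course of the scan will rule out subsequent statistical analysis". The two limits are joined by *and*.

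**Other motion handling.** Under Basic information for MRI scanning: "Head motion will be minimized by inserting special-purpose foam pads". The children also get used to the scanner beforehand and are asked to lie still. Preprocessing adds "head motion correction (a least squares approach and a 6-parameter spatial transformation"). The article states no other motion handling.

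**Imaging model (Statistical analysis).** The post-training index is the dependent variable, with "the group (MHRT, HRT, PST, and HC) as the independent variable and the baseline measure of the outcome as a covariate". The section adds: "We will also perform these analyses correcting for age, years of education and sex". Head motion is not among the covariates.

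**Intended use.** The Abstract treats changes in the network parameters as the neural correlates of training. Construction of the network plans to relate "the changes in these two brain functional networks and the improvements in tics and PUs". The Discussion predicts larger tic reductions under MHRT and HRT than under PST.

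**The concern.** Two features of the plan combine.

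1. Under the literal rule, a child with 6 mm of translation and 0.8° of rotation (an invented example) is kept, because only one limit is broken. The translation limit is also as large as one acquired in-plane voxel ("voxel size = 3.5 × 3.5 × 3.0 mm, and 36 axial slices"). That is not an error in itself, but it shows how much motion can remain among retained scans.
2. The group comparison has no term for the motion that remains. Motor tics are movements, so a treatment that reduces tics may also reduce movement during the second scan. That difference would arise after randomisation and through treatment, so random allocation does not prevent it. The baseline index captures only the part of the motion effect that was already present at the first scan.

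The imaging outcomes are built from Pearson correlations between time series, and the protocol's own use of padding, realignment and exclusion accepts that motion harms these data. If motion shifts the indices, it could produce both an arm difference in DMN and SN measures and a correlation between network change and tic improvement. Those two results carry the mechanism claim. Contrasts with healthy controls, who have no tic disorder, are exposed in the same way.

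**Working it through.** **1. The plan's own scan-loss figure.** Sample size estimation gives 23 per group, 20% drop-out and 15% invalid MRI data.
- 23 / (0.80 × 0.85) = 33.8, rounded up to 34. The stated 34 reproduces.
- With 40 recruited per group, 40 × 0.80 × 0.85 = 27.2, so about 27 per arm and 3 × 27 = 81 patients.
- If the 15% applies to each of the two scans independently, 40 × 0.80 × 0.85 × 0.85 = 23.1, so about 23 per arm and 3 × 23 = 69 pairs.

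**2. How much *and* versus *or* matters.** Assume that 15% of participants exceed each limit and that translation and rotation follow a bivariate normal distribution with correlation 0.3 to 0.8. Write P(both) for the joint exceedance.

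| Correlation | *and*: P(both) | *or*: 0.15 + 0.15 − P(both) |
|---|---|---|
| 0.3 | 4.2% | 25.8% |
| 0.8 | 9.1% | 20.9% |

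The two readings fall on opposite sides of the 15% allowed for in the sample size.

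**3. Group comparison with no direct network effect.** Two arms were simulated with 27 per arm, 4,000 runs and a two-sided 0.05 level. The post-training index was regressed on group and baseline index. Assumptions: motion and index have unit variance, scan-to-scan correlation is 0.49 for both, motion correlates *b* with the index, and post-training motion differs by *d* SD between arms. The upper *d* equals the pilot YGTSS effect size of 0.68, and the lower is half of that.

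| *d* | *b* | Rejection, planned covariate (baseline index) | Rejection, motion at both scans added |
|---|---|---|---|
| 0 | 0.3 | 4.9% | 5.1% |
| 0 | 0.5 | 4.9% | 5.0% |
| 0.34 | 0.3 | 7.2% | 5.5% |
| 0.34 | 0.5 | 11.1% | 5.1% |
| 0.68 | 0.3 | 13.0% | 4.8% |
| 0.68 | 0.5 | 27.5% | 5.2% |

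Hand check of the corners:
- Residual SD = √(1 − 0.49²) = 0.872, and SE = 0.872 × √(2/27) = 0.237.
- *d* = 0.34, *b* = 0.3: bias 0.102, ratio 0.102 / 0.237 = 0.43, normal-approximation rejection 7%.
- *d* = 0.68, *b* = 0.5: bias 0.34, ratio 0.34 / 0.237 = 1.43, normal-approximation rejection 30%, slightly above the simulated 27.5%.

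**4. Correlation of network change with tic change.** The article does not specify this test, so a pooled Pearson correlation across the three patient arms is assumed. If motion change correlates *a* with both changes and nothing else links them, the induced correlation is r = *a*². The test uses Fisher's z with SE = 1/√(n − 3), which is 0.123 for 69 pairs and 0.113 for 81.

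| *a* | Induced r | Fisher z | Rejection, 69 pairs | Rejection, 81 pairs |
|---|---|---|---|---|
| 0.2 | 0.04 | 0.040 | 6% | 6% |
| 0.4 | 0.16 | 0.161 | 26% | 30% |
| 0.5 | 0.25 | 0.255 | 55% | 62% |

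**The case against.** **The *and* may be loose wording.** The Preprocessing section is loosely phrased elsewhere, and the phrase can be read as a list of two separate limits. This stands as a reason not to say that a both-limits rule is intended. It does not remove the need to correct the text, because the readings keep different scans.

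**The article is condensed.** The preprocessing steps are introduced as inclusions, so nuisance regression of motion may sit in the full protocol or the software pipeline. This also stands: a reader might infer that motion is otherwise uncontrolled, and the article does not support that. It states padding, realignment and an exclusion rule. The covariate list of the group model, however, is fixed in the text and has no motion term.

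**The causal step is not shown.** A reader might infer that an effective arm will move less at the second scan, or that confounding has been demonstrated. The article has no data on motion or tics in the scanner, the YGTSS total counts phonic as well as motor tics, and the children are told to keep still. With equal motion across arms the planned test holds its level. The risk is plausible, not proven.

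**Post-training motion may itself be an effect of treatment.** Adjusting for it can remove part of a real effect. This is correct, and it is why the adjusted model belongs beside the planned one as a sensitivity analysis and not in its place.

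**Conclusion.** The point holds in this form. The exclusion rule as worded keeps a scan that is far over one limit, and the stated imaging model has no head-motion term, so a motion difference that arises after randomisation could be read as a neural correlate of training.

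The size cannot be derived from the article. Under the assumptions shown, the planned group comparison rejects in about 7% to 28% of trials with no direct network effect, against 5% when motion is equal across arms. For an assumed pooled correlation, rejection runs from about 6% when motion correlates 0.2 with both changes to 55% to 62% when it correlates 0.5. The upper figures should not be quoted without the lower ones.

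The imaging outcomes are secondary, and nothing here touches the YGTSS comparison. They do carry the whole mechanism claim, so the change is worth making.

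**What to change.** 1. Confirm which rule was meant, and state the exclusion as either limit exceeded at either scan.
2. Compute mean framewise displacement for each scan from the six realignment parameters already estimated, and report it by arm (including healthy controls) and visit.
3. Keep the planned group models and brain-symptom correlations. Beside each, show a sensitivity version with motion as a covariate, either baseline and post-training values or their change.
4. Claim a network effect beyond motion only if it survives in the adjusted version.
5. If nuisance regression of motion is already part of the full protocol, say so in the text.

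**Cost.** No new data and little extra analysis. An either-limit rule may lose more scans than the 15% allowed for in the sample size (about 21% to 26% under the assumption in step 2 of the working). Adjusting for post-training motion may absorb some true effect, which is why both versions are reported.
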